### Sample size calculation

The sample size was determined to achieve 90% power to declare non-inferiority of magnesium hydroxide in case the proportion of patients with a score < 30 on the BFI at day 14 to be equal for magnesium hydroxide and macrogol/electrolytes assuming one-sided testing at a significance level of 2.5% [30]. The sample size was based on two non-randomized studies that showed that approximately 40% of patients starting with opioids and not using laxatives do not develop constipation after 14 days [31, 32]. Prophylaxis with laxatives can only be effective in (part of) the remaining 60% of patients. Treatment with macrogol/elektrolytes is effective in 70% of patients with symptomatic chronic constipation [33, 34]. Based on these data, we estimated the percentage of patients without constipation (BFI < 30) after 14 days of treatment with macrogol/electrolytes to be 82% (40% plus 0,7 × 60%). The main considerations are that the proportion of patients with a BFI < 30 under magnesium hydroxide at the non-inferiority margin should clearly be higher than the estimated 40% of patients without opioid induced constipation and the clinical judgement that more than 15% difference could no longer be translated in a conclusion that magnesium hydroxide is non inferior to macrogol/electrolytes. Based on the previous data, we calculated a sample size of 138 evaluable patients per arm. We will increase the inclusion with approximately 20% to anticipate potential loss to follow-up to N = 165 per arm.

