### Statistical analysis

All data will be coded and collected in a secure cloud-based clinical data management platform (Castor EDC). Analysis will be performed using the latest version of IBM SPSS Statistics.

Primary analysis for non-inferiority will be performed both on a protocol and intention-to-treat basis. The primary outcome is the difference in proportion of responders (BFI < 30 at day 14) between the two arms. The primary analysis will use the Newcombe score method to estimate a one-sided 97.5% confidence interval for the difference in proportion of responders (proportion responders under magnesium hydroxide minus proportion responder under macrogol/electrolytes). The null hypothesis (H0: Magnesium hydroxide is inferior to macrogol/electrolytes in the prevention of OIC) will be rejected and non-inferiority will be claimed for magnesium hydroxide if the lower boundary of the 97.5% confidence interval is larger than the prespecified non-inferiority margin of -15%. An additional analysis will be performed in which the risk difference for response is estimated using a generalized linear model for a binomial outcome and an identity link, while adjusting for the stratification factors of center and constipation at the start of the study.

An additional per protocol analysis will be performed using inverse-probability-of-treatment-weighing (IPTW) in the intention-to-treat population. For this IPTW analysis, logistic regression analysis in the intention-to-treat population will be used to predict the probability of a subject being adherent based on predefined confounders. In this analysis, non-adherence is defined as < 80% of the prescribed laxative being taken as determined from the patient diary [35]. The inverse of the predicted probabilities will then be used as weights in an analysis comparing treatment outcomes between the groups and to estimate a per-protocol effect. In this weighted analysis, the risk difference for response and its two sided 95% confidence interval is estimated using generalized linear models for a binomial outcome and an identity link, while adjusting for the stratification factors.

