A scenario will be added to the analyses for the use of naloxegol and naldemedine as a first-line treatment in case of OIC. Naloxegol and naldemedine are peripheral µ-receptor antagonists that have shown to be effective for the treatment of OIC [36]. There are no studies available yet evaluating the efficacy of naloxegol for prevention of OIC. For naldemedine there is one recent randomized controlled trial available that has evaluated the efficacy of naldemedine for prevention of OIC [10]. As no effect data of first-line treatment with naloxegol or naldemedine will be measured during the trial, the scenario analysis will be an early health-economic analysis. In this analysis we will use effect data based on literature and expert opinion and will perform a threshold analysis to estimate the effect size needed to result in a cost-effective intervention. Bootstrapping will be performed to assess the uncertainty of costs and utility loss of (sub)groups, while deterministic (one-way) and probabilistic sensitivity analyses will be performed to assess the uncertainty of the analyses in the decision tree.

With regards to missing data, we do not plan imputation for the main outcome. If unexpectedly outcomes are missing, we will perform sensitivity analyses using single-value imputation under the most extremes scenarios. Multiple imputation may be considered if important confounders are missing or if missing on the main outcome is higher than currently anticipated.

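### Missing day-14 outcomes are called unexpected although the plan budgets for 16.4% loss per arm, and at that loss the committed extreme-case checks cannot tell a robust non-inferiority result from a fragile one

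*Protocol article*

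**What the plan says.** All references are to the protocol article.

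- **Statistical analysis, missing data, main rule.** On imputation: "we do not plan imputation for the main outcome".
- **Same paragraph, check.** "If unexpectedly outcomes are missing, we will perform sensitivity analyses using single-value imputation under the most extremes scenarios". The scenarios are plural and are not listed.
- **Same paragraph, further option.** Multiple imputation may be considered in two situations: important confounders are missing, or more primary outcomes are missing than anticipated.
- **Sample size calculation.** "We will increase the inclusion with approximately 20% to anticipate potential loss to follow-up to N = 165 per arm". The starting figure is 138 evaluable patients per arm.
- **Statistical analysis, primary analysis.** Non-inferiority is analysed both per protocol and by intention to treat. It is claimed if the lower limit of the one-sided 97.5% Newcombe interval (magnesium hydroxide minus macrogol/electrolytes) lies above -15 points. The missing-data scenarios have no stated role in that decision.

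**The concern.** Loss of about one patient in six cannot be both budgeted in the sample size and unexpected in the analysis. If no outcome is imputed and no other rule applies (for example, missing counted as non-response), patients without a day-14 Bowel Function Index (BFI) leave the intention-to-treat comparison. In a non-inferiority trial this can flatter the new treatment if the missing magnesium hydroxide patients do worse than those observed. The trial is open-label, so loss may differ between arms.

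The reader then depends on the sensitivity analysis, and the only one the plan commits to is the set of extreme scenarios. If these give nearly the same pass/fail pattern whether or not the result is sound, the primary claim rests on complete cases with no informative check. Outcome loss at the budgeted level does not trigger the more graded method, multiple imputation.

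**Working it through.** **Inputs.** From Sample size calculation: 82% response on macrogol/electrolytes, assumed "to be equal for magnesium hydroxide and macrogol/electrolytes"; power 90%; one-sided alpha 2.5%; 138 evaluable and 165 randomised per arm. From Statistical analysis: margin -15 points, Newcombe score interval.

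**1. The plan's own sample size.**
n = 2 × 0.82 × 0.18 × (1.960 + 1.282)² / 0.15² = 137.9, so 138 per arm. This reproduces. For loss, 138 × 1.2 = 165.6, in line with the stated 165. The allowance is 165 - 138 = 27 per arm, and 27/165 = 16.4%.

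**2. Interval used.** With Wilson limits (l, u) for each proportion at z = 1.96, the Newcombe lower limit is
d - √[(p₁ - l₁)² + (u₂ - p₂)²], where arm 1 is magnesium hydroxide.

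**3. Scenarios at the budgeted loss.** 0.82 × 138 ≈ 113 observed responders per arm and 27 missing per arm. Probabilities of passing come from exact enumeration of two independent Binomial(138, 0.82) counts.

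| Handling of the missing | Mg hydroxide | Macrogol | Difference (points) | Lower limit (points) | Probability of passing |
|---|---|---|---|---|---|
| Complete cases | 113/138 | 113/138 | 0 | -9.1 | 90.2% |
| Extreme against Mg hydroxide | 113/165 | 140/165 | -16.4 | -25.2 | 0.35% |
| Extreme for Mg hydroxide | 140/165 | 113/165 | +16.4 | +7.3 | about 100% |
| All failures, both arms | 113/165 | 113/165 | 0 | -9.9 | 90.9% |
| All responders, both arms | 140/165 | 140/165 | 0 | -7.8 | 96.8% |

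For the second row: p₁ = 0.6848, l₁ = 0.6104; p₂ = 0.8485, u₂ = 0.8952. The limit is -0.1636 - √(0.0744² + 0.0467²) = -0.1636 - 0.0879 = -0.2515.

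With equal observed rates and 27 missing in each arm, the difference in that row is -27/165 whatever the common response rate. The point estimate alone is beyond -15. The chance of passing is 0.8% at a common rate of 60% and 0.08% at 90%.

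**4. Where the unfavourable extreme starts to fail (expected counts at 82%).**
- 10 missing per arm (6.1%): 127/165 v 137/165, lower limit -14.6, passes.
- 11 missing per arm (6.7%): 126/165 v 137/165, lower limit -15.3, fails.

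To pass with 27 missing per arm and 113/138 observed on macrogol/electrolytes, magnesium hydroxide would need 130/138 (94.2%) observed responders.

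**5. Unequal loss.** With 54 losses in total and both drugs at 82%, the unfavourable extreme passes with these probabilities (magnesium hydroxide v macrogol losses): 34 v 20, 0.03%; 20 v 34, 2.8%; 10 v 44, 22%; 0 v 54, 64%.

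**6. What a graded analysis would show.** As a simple illustration that ignores imputation uncertainty, count the missing macrogol patients at 82% (22 of 27), giving 113 + 22 = 135/165. Then lower the number of responders among the 27 missing magnesium hydroxide patients:
- 12 of 27 (44%): 125/165 v 135/165, lower limit -14.8, non-inferiority holds.
- 11 of 27 (41%): 124/165 v 135/165, lower limit -15.4, non-inferiority is lost.

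This can be judged clinically: the result would turn at about the plan's own 40% figure for patients without a laxative.

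**The case against.** The strongest reply is that the plan is tiered: complete cases, then bounds, then multiple imputation if loss is larger. Worst-case and best-case imputation is meant to bracket the result, and a wide bracket at 16% loss is an honest answer. At low loss the bounds do inform; on expected counts even the harshest passes up to 10 missing per arm. Scenario definitions and imputation models also commonly belong in the analysis plan, which is not shown. Much of this stands, and it rules out several stronger readings that a reader might infer.

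- *The sensitivity analysis must fail even if the drugs are identical.* Not supported. The plan speaks of several scenarios, and only the extreme against magnesium hydroxide nearly always fails. The point estimate is sure to breach the margin only with equal observed rates and balanced loss; otherwise failure is a probability.
- *Extreme imputation is the only method mentioned.* Not so. Multiple imputation is named, but as an option. Extreme imputation is the only check committed to.
- *Patients who stop the laxative for side effects vanish from the analysis.* The documents do not say this. The Treatment section allows stopping during the study, and the day-14 BFI is taken by telephone, so stopping treatment is not the same as a missing outcome.
- *A failed scenario defeats the claim.* No such rule is stated; the claim rests on the primary interval.
- *Multiple imputation must become primary.* This is debatable. BFI is measured only on days 0 and 14, diaries may be unavailable for patients lost to follow-up, and standard multiple imputation assumes missingness at random, so it does not by itself deal with informative loss.

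The reply does not remove the conflict between unexpected and budgeted loss. Nor does it answer that, at the anticipated loss, the committed bounds are too wide to inform. Both follow from what the article states, not from detail it leaves out.

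**Conclusion.** The concern holds in a limited form. The article treats as unexpected a loss that its sample size anticipates at 27 of 165 per arm. The intention-to-treat analysis is in effect complete-case, and at that loss the committed extreme bounds do not separate a robust result from a fragile one: one passes with probability 0.35% and the other with near certainty when the drugs are identical.

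These figures assume 82% response in both arms, 27 missing in each arm, and missingness unrelated to outcome among those observed. If loss falls mainly on macrogol/electrolytes, the unfavourable extreme passes more often. If all missing are set to the same value in both arms, non-inferiority is usually kept.

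The sample size of 138 is not at fault, and nothing here shows that the primary estimate will be biased. The weakness is that, at the loss the plan foresees, readers would have no committed analysis with which to judge whether it is.

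**What to change.** 1. Delete the word that makes missing outcomes unexpected, and state that they are anticipated at up to the budgeted rate (27 of 165 per arm).
2. Commit in advance to a delta (tipping-point) analysis at whatever loss occurs. Start from multiple imputation by arm, using baseline BFI, centre and any available diary data. Then lower the assumed response of missing magnesium hydroxide patients relative to missing macrogol/electrolytes patients in fixed steps until non-inferiority is lost.
3. Keep the extreme scenarios as outer bounds only, and list them.
4. State how the tipping point bears on the non-inferiority conclusion, for example by fixing beforehand which response rates among the missing are regarded as plausible.

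Making multiple imputation the primary analysis is optional. The cost is a few sentences in the protocol or analysis plan and modest programming. Baseline BFI, centre and the diary are already collected, though diary data may be incomplete for patients lost to follow-up. The change should be made before outcome data are analysed.

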## Discussion

The OMAMA study is an open-label, randomized controlled trial that examines if magnesium hydroxide is non-inferior to macrogol /electrolytes in the prevention of opioid-induced constipation (OIC) in patients with metastatic or locally advanced incurable cancer. OIC is a symptom that often occurs in palliative care and can have a negative impact on the quality of life of patients. In current practice both macrogol/electrolytes and magnesium hydroxide are prescribed for the prevention of OIC. Yet, scientific evidence in the form of randomized controlled trials is largely lacking. The OMAMA study will provide evidence on the prevention of OIC, the tolerability and side-effects of both laxatives.

Research in palliative patients can be challenging and has been controversial for a long time. Often the ethical concern is whether it is morally justified to let these patients participate in research [37, 38]. They are considered vulnerable and fragile due to their illness and/or multiple co-morbidities with a high risk of drop-out [39]. However, multiple studies showed that palliative patients are willing to participate in medical research and may benefit from their participation [37, 39, 40]. Nonetheless, it is important to minimize the burden when conducting research with this group of patients [41]. In our study the extra burden for the patient will be minor. If the patient does not participate in the study, the physician will also prescribe either macrogol/electrolytes or magnesium hydroxide (depending on the treating physician or the protocol of the hospital) to prevent constipation. Furthermore, the study period is only fourteen days during which patients will have to complete the questionnaires only at the beginning and at the end of the study period. During the process of writing the study protocol and standard operating procedures we have asked two cancer patients for comments and for help to minimise the burden for the patient.

There is relatively little time given to the patient for the informed consent. Patients in the outpatients clinic will be asked for informed consent after the consult with their physician and hospitalized patients will be asked informed consent within 24 h after starting with opioids. However, waiting longer with starting a laxative may be detrimental to the patient. Moreover, our study is a low-intervention trial and as stated above, the burden for the patient will be minor.

Our study period of fourteen days is based on previous studies which show that it is sufficient time to evaluate the development of constipation [10, 31, 32]. Two prospective non-randomized studies compared the incidence of OIC after 14 days with or without prophylactic laxatives and found an incidence of 48% [31] and 34% [32] in the group treated with prophylactic laxatives versus an incidence of 65% [31] and 55% [32] in the group treated without prophylactic laxatives, respectively. They concluded that prophylactic laxatives were associated with a lower incidence of OIC. These data suggest that approximately 60% of patients starting with opioids and not using laxatives will have developed constipation after 14 days and 40% will not. Moreover, studies have shown that a single administration of opioids can already cause constipation [42–44]. Consequently, after 14 days of therapeutic opioid doses it will be possible to evaluate if a patient has developed constipation or not.

In this study we have not included a placebo treatment group, because the aforementioned studies already have shown that approximately 60 percent of the patient starting with opioids will develop constipation when no laxative is prescribed [31, 32]. Therefore, a placebo arm was thought to be unethical.

Our study has some limitations. First of all, our study focuses on a specific patient group (i.e. opioid-naive patients with incurable cancer) and the question may arise whether the results can be extrapolated to non-cancer patients. However, cancer patients might have OIC that is more difficult to treat than OIC in non-cancer patients, due to additional factors contributing to constipation. These factors include tumor growth in the gastrointestinal tract, decreased mobility, inadequate oral intake of fluids and dietary fibers and use of other constipation-inducing drugs such as antiemetics and anticholinergic drugs [45, 46]. Moreover, most cancer patients are elderly, who already have reduced colonic motility due to changes caused by aging [47]. Hence, if prevention of OIC with either laxative is successful in these cancer patients, it will probably also be successful in non-cancer patients.

Another limitation is that the EQ-5D-5L that is used in this study is a general tool to measure the quality of life. There exists a more specific, but much more extensive tool to measure quality of life related to constipation, the Patient Assessment of Constipation Quality of Life (PAC-QOL) [48]. The PAC-QOL consists of 28 questions. Since the patients already have to complete various other questionnaires, it was thought that adding this questionnaire would increase the burden on the patient and potentially increase the chance of missing data. Furthermore, the EQ-5D is a commonly used tool in cost-effectiveness analyses [49].

## Conclusion

The OMAMA study will evaluate if magnesium hydroxide is non-inferior to macrogol/electrolytes in the prevention of opioid-induced constipation in patients with metastatic or locally advanced incurable cancer. Both laxatives are commonly used as a preventive medicine, yet scientific evidence is scarce. Our study will provide evidence on the prevention of OIC and will compare the tolerability and side-effects of both laxatives. The OMAMA study has started recruitment in October 2022 and is expected to be completed in 2 years.

## Data Availability

Not applicable.

## Abbreviations

OIC: Opioid-induced constipation
GCP: Good Clinical Practice
ICH: International Conference of Harmonization
PIL: Patient information leaflet
BFI: Bowel Function Index
EQ-5D-5L: 5-Level EuroQol-5 Dimension
iMCQ: iMTA Medical Consumption Questionnaire
EMA: European Medicines Agency
IPTW: Inverse-probability-of-treatment-weighting
NZa: Nederlandse Zorgautoriteit (Dutch Healthcare Authority)
PAC-QOL: Patient Assessment of Constipation Quality of Life
